**14. Unanticipated Problems Involving Risks to Subjects or Others**

## 14.1 Definition of Unanticipated Problems Involving Risks to Subjects or Others (UPIRTSO)

The Office for Human Research Protections (OHRP) considers unanticipated problems involving risks to participants or others to include, in general, any incident, experience, or outcome that meets **all** of the following criteria:

- Unexpected in terms of nature, severity, or frequency given (a) the research procedures that are described in the protocol-related documents, such as the Institutional Review Board (IRB)-approved research protocol and informed consent document; and (b) the characteristics of the participant population being studied;
- Related or possibly related to participation in the research (“possibly related” means there is a reasonable possibility that the incident, experience, or outcome may have been caused by the procedures involved in the research); and
- Suggests that the research places participants or others at a greater risk of harm (including physical, psychological, economic, or social harm) than was previously known or recognized.

### **14.1.2 Unanticipated Problem Reporting**

The investigator will report unanticipated problems (UPIRTSOs) to the reviewing Institutional Review Board (IRB) and to the Data Coordinating Center (DCC)/lead principal investigator (PI). Further details of the UPIRTSO report are included in the SOP. The UPIRTSO report will include the following information:

- Protocol identifying information: protocol title and number, PI’s name, and the IRB project number;
- A detailed description of the event, incident, experience, or outcome;
- An explanation of the basis for determining that the event, incident, experience, or outcome represents an UPIRTSO;
- A description of any changes to the protocol or other corrective actions that have been taken or are proposed in response to the UPIRTSO.

To satisfy the requirement for prompt reporting, UPIRTSOs will be reported using the following timeline:

- UPIRTSOs that are serious adverse events (SAEs) will be reported to the IRB and to the DCC/study sponsor within 7 days of the investigator becoming aware of the event.
- Any other UPIRTSO will be reported to the IRB and to the DCC/study sponsor within 7 days of the investigator becoming aware of the problem.
- All UPs should be reported to appropriate institutional officials (as required by an institution’s written reporting procedures), the supporting agency head (or designee), Food and Drug Administration (FDA), and the Office for Human Research Protections (OHRP) within 24 hours of the IRB’s receipt of the report of the problem from the investigator.

# 15. Data and Safety Monitoring Plan (DSMP)

**Data safety monitoring plan for:** Reducing Obesity Using Social Ties (ROBUST)

**Principal Investigator:** [name], MS

**Grant Application #:** 1R01DK135949-01

Overall the intervention and measurement protocols pose minimal risk to the index participants and their participating social network members. Because of this low-risk status, the data safety monitoring (DSM) plan for this trial focuses on close monitoring by the principal investigator (PI) in conjunction with a safety officer ([name]), along with prompt reporting of excessive adverse events and any serious adverse events to the NIH and to the IRB at the Weill Cornell Medicine.

Although there are additional reports to be produced by the study coordinator as a result of this DSM plan, there are no substantive changes to the study protocol that might require review by the NIDDK. Safety reports will be sent to the study statistician, the PI, and the safety officer. The Program Manager will be responsible for assembling the data and producing these reports, as well as assuring that all parties obtain copies of these reports.

The frequency of data review for this study differs according to the type of data and is summarized in the following table:

| **Data type** | **Frequency of review** |
| --- | --- |
| Subject accrual (adherence to protocol regarding demographics, inclusion/exclusion) | Bi-annually (mid-point and end of each  study year period) |
| Adverse event rates (injuries) | As they occur |
| Intervention fidelity and adherence | Bi-annually (mid-point and end of each  study year period) |
| Stopping rules report regarding statistical power implications of dropouts and missing data | Yearly |

## Data Quality and Management

Using an Internet based system, such as REDCAP raises issues of data privacy and security. REDCap is a mature, secure web application for building and managing online surveys and databases. REDCAP has procedures and technology to restrict access to only trusted local sites. Identification of trusted sites and standard password protection techniques are employed. In addition, all data, including passwords, are encrypted using state of the art encryption software before passing across the Internet. REDCAP is fully HIPAA compliant: all users must have secure passwords of sufficient complexity that are automatically prompted to change every predefined interval. All patient privacy information is typically stored in one location (the HIPAA form), the access to which is strictly limited. The security of *REDCAP* is only part of the security of the web server (SSL encryption) and computer system being used. The servers that house *REDCAP* run SE Linux (security enhanced; the same as that used by the National Security Agency), are all password protected, are regularly backed up, and well protected. Each user entering data on the system will have security identification and specific access rights. All data will be linked to the user that entered it as well as the timestamp of data entry. After the initial data has been entered into a record, any subsequent changes of the data will be entered into a special log file and reviewed by the data management team. A complete audit trail is also built into the system: this tracks who changed what data and when. The system has multiple levels of access rights (defined as what data users are allowed to have access to) and different levels of access permission (defined as the specific use allowed to the data being accessed). Each user entering data on the system has a security identification and specific access. For example, with respect to access rights, some users would have access rights only to demographic data, but not to clinical data. With respect to access permission, some users would be given access permission only to view, but not to add, edit or delete data. Other users may have rights to add, edit, delete or view data. The data management team ([name], data analyst and coordinator) will establish which project members will have access and what their permission level will be.

To ensure high-quality data, in addition to range checks embedded in the RedCap forms, the research staff will review data on a weekly basis. We will investigate any data irregularities, including missing data. Monthly, they will meet with the study PI to review study data management. Any inconsistencies will lead to data queries to be resolved by the data analyst and study statistician.

In the event of an audit all requested documents will be made readily available to the regulatory body.

Protection of the participant’s privacy and confidentiality:

There is a potential risk to the participant with regards to possible violation of their privacy. We have taken steps to avoid this by making sure that only investigators on the study have access to a password protected data file. All investigators and research assistants will be required to fulfill all requirements of the institution for HIPPA and IRB training. As part of the process involved in obtaining written informed consent, all participants will be reminded that their responses are confidential and that they may refuse to participate in the project or withdraw at any time without explanation, and further, that such action will in no way affect their future interactions with their health care provider. Study data will be transmitted to the data management team for data processing using only secure methods (e.g., encryption). Prior to inclusion in any data set (internal and external), data will be stripped of all identifying information.

## Qualifications and responsibilities of the Safety Officer

The safety officer for this trial will be [name], MPH, MS. [name] is a practicing, board-certified general internist and a health services researcher in the Division of General Internal Medicine at Weill Cornell Medicine. She has formal training in cardiovascular clinical epidemiology, health services research (qualitative and quantitative research methods), community-engaged intervention-design, and the conduct of real-world clinical trials. She is currently PI of two community-based clinical trials, one of which involves a lifestyle intervention (NHLBI-K23HL150160; Doris Duke Clinical Scientist Award – 2022053). As such, she has an understanding of the types and severity of injuries commonly experienced as a result of lifestyle intervention. As Safety Officer, [name] will review the reports sent by the study coordinator (at the frequency previously outlined) and will use the checklist attached to this document to determine whether there is any corrective action, trigger of an ad hoc review, or stopping rule violation that should be communicated to the study investigator, the Weill Cornell IRB, and the NIDDK.

## Measurement and reporting of subject accrual, adherence to inclusion/exclusion criteria

Review of the rate of subject accrual, adherence to inclusion/exclusion criteria will occur bi- annually (mid-point and end of each study year). This review will ensure that participants meet eligibility criteria and ethnic diversity goals outlined in the grant proposal. Based on our clinical trial milestone plan we anticipate the following accruals will have taken place at each data review.

| **Milestone #** | **Description** | **Date** |
| --- | --- | --- |
| 1 | Hire and train study staff | *Yr 1, Q2* |
| 2 | *Randomization and enrollment of 25% of participants and alters* | *Yr 1, Q4* |
| 3 | *Randomization and enrollment of 50% of participants and alters* | *Yr 2, Q2* |
| 4 | *Randomization and enrollment of 100% of participants and alters* | *Yr 2, Q4* |
| 5 | *Follow up visit completion of 100% of participants and alters; primary data collection on study participants completed; completion of close out assessment* | *Yr 3, Q2* |
| 6 | *Clean up assessment data for analysis of secondary endpoints and complete end of study summary/ data safety monitoring plan* | *Yr3, 4* |

## Measurement and reporting of adverse events

We plan to collect symptom data related to increased physical activity and adverse events as part of the routine coaching sessions at week 3, 4, 5, 7, 9, 11, 13, 15, and 20. We plan to present unblinded adverse events data to the study statistician, the PI, and the safety officer throughout this trial. There is some level of injury expected from individuals potentially increasing their physical activity although the recommended mode of physical activity will be walking and reducing sedentary time. In our previous RCT study of 405 adults enrolled in a lifestyle intervention study and followed over 12 months, 13 (16%) expected adverse events (were likely related to the study protocol. Among all AE's, 17 (21%) were related to musculoskeletal complaints. There were 7 (9%) cardiovascular events and 17 (21%) pulmonary events. 73% of the total adverse events (81) were rated as unlikely or unrelated to the intervention. ^28^

Definitions of expected adverse events for this study:

*Cardiovascular, pulmonary, hypoglycemia:* Adverse events will be defined as cardiovascular (MI, CVA, death), acute shortness of breath, or hypoglycemia precipitated by changes in dietary intake or the physical activity chosen for the study requiring hospitalization/emergency room visit or a physician office visit. Non-routine office visits for cardiac or pulmonary disease or diabetes are expected and not serious unless they lead to the above events.

*Major depressive episode or anxiety attack:* Infrequent likelihood. A participant may become depressed, anxious or severely embarrassed if friends/family/acquaintances find out that the person is participating in and/or not losing weight in the program. Patients have the option of not answering any questions they do not want to. As this is a voluntary study, a participant is free to withdraw from the study at any point if they feel uncomfortable or do not want to continue.

*Medication Side Effects* Infrequent risks. The study does not prescribe medication. Weight loss can cause a change in the dose of medication needed to treat common health conditions such as hypertension, diabetes and hypothyroidism. Participants will be required to communicate their participation in the study along with their weight loss to a primary care physician.

*Musculoskeletal*: Musculoskeletal injury due to the physical activity chosen for this study resulting in hospitalizations, emergency department visits, or treatment for fracture in any setting will be considered expected serious adverse events. Non-routine office visits for musculoskeletal injury are expected and not serious unless lead to the above events. Temporary minor incapacitation due to muscle soreness is also expected and not serious.

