### **6.1.2 Treatment Phase**

Eligible participants will be randomly assigned to the social network intervention or control groups in a 1:1 ratio using a numerical randomization scheme developed by the statistical team. Following randomization, participants that are randomized to the social network intervention group will complete 3 in person communication skills sessions with their social network members during weeks 3, 5, and 15. Instead of completing communication skills sessions, participants randomized to the control group will complete regular virtual lifestyle coaching sessions with the study team that consists of the following topics: Keep your health healthy (week 3), Eat well away from home (week 5), and Social Cues (Week 15). All other sessions will focus on the topics below and will be the same across both treatment groups.

Note: The weeks that are not listed in the treatment phase below are weeks that will be treatment breaks.

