## 7.11 Measures to Minimize Bias: Randomization and Blinding

Index participants will be randomized after completion of the social network interview either to the ROBUST intervention or lifestyle intervention, using a random number generator. All index participants, regardless of randomization group, will complete a social network interview to characterize their personal network prior to randomization. The same social network interview will be conducted at 24 weeks. All participants will also receive the same number of coaching sessions, as shown in **Table 1**. They will attend four sessions in person (baseline, week 8, week 16, and week 24), and the remaining 11 sessions will be conducted as a virtual visit. The in-person visits will occur at the Weill Cornell Clinical and Translational Science Center's dedicated research facility. During the in-person sessions, the participant will receive 1:1 dietary counseling with a registered dietician who has been trained on the study protocol. The study research staff complete anthropometric measurements (height, weight, and body composition). Participants randomized to the intervention group will be expected to attend virtual visits at weeks 3, 5, and 15 with their social network member.

Consenting of study participants as well as all study assessments (i.e. baseline, 8 ,16 & 24 weeks) will be conducted by an assessor who is not responsible or involved in the delivery of the coaching sessions, dietary counseling or communication skills sessions. While the study PI & co-investigators will be blinded, the same will not be possible for the trained coach delivering the intervention. Due to budget limitations, having two coaches (i.e. one for the control group and for the intervention group) is not feasible. Since the communication skills training sessions are designed to occur between the index participant and consented social network members, the implication of contamination is reduced as control group participants will not have any consented social network members participating in the study.

*.*

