## Measurement and reporting of participant compliance to treatment protocol:

Session attendance will be measured as a marker of adherence, with a benchmark of attending at least 75% of the coaching/assessment sessions for both index participants (11 out of 14) and social network members (3 out of 4). 'Treatment (intervention) fidelity' will be assessed in three ways. The first is a checklist in REDCAP that the coach will complete at the end of each session. This checklist will also serve as a reminder to the coach about the active ingredients to be delivered during the session. The second method is a monthly review of a random sampling of 10% of the coaching sessions. Points will be given for each required treatment element delivered correctly and subtracted for any contamination elements. If the average fidelity falls below 90%, the coach will be retrained. The third is by each tracking the session duration in minutes. The coach will assess enactment fidelity at the beginning of each coaching session using a simple yes/no checklist. This data will be reviewed in bi-weekly team meetings (study coordinator, PI and interventionists) and reviewed by the safety officer bi-annually. If the safety officer has concerns about whether intervention fidelity has reached a level that might inhibit the ability of the study to test its primary hypotheses, she will suggest a conference call for study investigators to discuss methods for improving study adherence.

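### Section 7.11 says the PI is blinded, but the safety monitoring plan gives the PI unblinded adverse-event data throughout the trial

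*Protocol*

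**What the plan says.** Protocol Section 7.11, on measures to minimise bias, states: "While the study PI & co-investigators will be blinded, the same will not be possible for the trained coach delivering the intervention". The coach is the only exception it names. It also has consent and all study assessments done by a person who takes no part in delivering the sessions.

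Section 15 (the data and safety monitoring plan) describes a different flow of information:

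- On adverse events: "We plan to present unblinded adverse events data to the study statistician, the PI, and the safety officer throughout this trial".
- On routing: "Safety reports will be sent to the study statistician, the PI, and the safety officer". The review table in the same section has adverse-event rates looked at whenever events arise, not at fixed intervals.
- On fidelity and compliance: "This data will be reviewed in bi-weekly team meetings (study coordinator, PI and interventionists) and reviewed by the safety officer bi-annually".
- Under stopping rules, the safety officer and the study investigators jointly alert the IRB and the NIH if the treatment group shows more events than expected.

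**The concern.** Blinding of the PI and co-investigators is offered as a safeguard against bias. If the monitoring plan is followed, the PI does not have that safeguard, yet a report that repeats Section 7.11 would claim it.

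What is at stake is investigator discretion. Section 8.2 lets an investigator withdraw a participant for significant non-compliance with the intervention. Such a withdrawal bears on completion of the final assessment (the 85% primary endpoint), on the retention rate, and on the comparison of dropout between arms in Section 12.4.1. It can also change who enters the completers-only analysis in Section 12.4.2. A judgement about what counts as significant non-compliance is open to influence if the person making it knows the arm or has seen by-arm results.

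**Working it through.** No figure has to be reproduced and no arithmetic applies. The check is whether the statements can all be true together.

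**1. Scope of the blinding claim.** Section 7.11: "While the study PI & co-investigators will be blinded". The claim has no qualifier. It is not limited to outcome data and makes no exception for safety data.

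**2. Scope of the access.** The adverse-event section of the monitoring plan names the PI as a recipient, calls the data unblinded, and sets the period as the whole trial. In a two-arm trial, unblinded data are data that show allocation, whether by participant or as rates by arm. Either form is inconsistent with an unqualified statement that the PI is blinded.

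**3. Do other places limit the access?** They do not; they fit it. The opening of Section 15 sends the safety reports to the same three roles, with adverse events reviewed as they arise. The stopping rules have the study investigators act on the event rate in the treatment group specifically, which supposes that they know results by arm. This last text is also the only one that draws in the co-investigators; the adverse-event sentence names the PI alone.

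**4. Do the fidelity meetings add to it?** The PI meets bi-weekly with the interventionists, who are unblinded. Section 6.1.2 gives the two arms different sessions at weeks 3, 5 and 15 and says of the rest: "All other sessions will focus on the topics below and will be the same across both treatment groups". On fidelity scoring, the plan says: "Points will be given for each required treatment element delivered correctly and subtracted for any contamination elements". To score contamination one has to know which arm the session belonged to. Unblinding at these meetings is therefore plausible. It remains an inference, for three reasons:

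- The text does not say that data are shown by participant or by arm.
- The data referred to come directly after the enactment checklist and may not include every fidelity measure.
- The session review covers a random 10% sample.

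**5. Result.** Steps 1 and 2 alone establish the contradiction for the PI. Step 3 shows that nothing resolves it. Step 4 is supporting only.

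**The case against.** The strongest reply is that this is a wording conflict of small consequence in a minimal-risk behavioural trial. Much of that stands. A person outside delivery does the assessments, and weight is measured objectively. The primary endpoints are feasibility thresholds summarised mostly descriptively, and their network-member components exist only in the intervention arm. Whether the PI of such a trial should be blinded at all is a matter of preference. The protocol, however, has stated its preference and then planned against it. The assessor, moreover, is described as independent of delivery, not as blinded.

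Four stronger readings are tempting, and the document does not support them:

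- *That the statistician's access also contradicts Section 7.11.* The protocol never says the statistician is blinded, and Section 6.1.2 has the statistical team develop the randomisation scheme. That access would conflict only if the statistician counted as a co-investigator, which is not stated.
- *That the meetings reveal every participant's arm.* The presentation of the data is not described, as set out in the working.
- *That an expected number of adverse events measures the problem.* A count could be projected from the earlier trial cited in Section 15, but a count of events is not a bias in any endpoint.
- *That the dropout alerts are distorted by knowledge of arm.* They are set on dropout rates with no arm specified, and they lead to conference calls.

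It is also fair to say that by-arm rates would not necessarily identify individual participants. That softens the consequence but does not make the PI blinded.

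**Conclusion.** The point holds for the PI. Section 7.11 and the monitoring plan cannot both be carried out, and the protocol claims a safeguard that its own procedures remove. For the co-investigators the conflict is less direct and rests on the stopping-rule text.

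No size can be put on any resulting bias from this document. The credible route is discretionary withdrawal for non-compliance, acting on retention and on the dropout comparison; its extent is unknown. Impact on measured outcomes should be limited by the separate assessor, and impact on the primary feasibility endpoints by their mostly descriptive analysis. The conclusion assumes that unblinded carries its ordinary meaning of showing allocation. It does not depend on how bi-weekly is read or on what the fidelity meetings display.

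**What to change.** Reconcile Section 7.11 with four places in Section 15: the routing of safety reports, the adverse-event reporting, the compliance reporting and the stopping rules. There are two ways to do it.

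1. **Keep the blinding.** Send by-arm adverse-event data to the safety officer only. Give the PI pooled safety data and arm-masked fidelity summaries. Amend the stopping rules so that the safety officer makes the by-arm judgement and escalates. The Program Manager already assembles the reports, and the safety officer already has a line to the investigator, the IRB and the NIDDK, so the structure exists. The cost is that the PI sees by-arm safety data only on escalation and steps back from session-level fidelity review, in a plan that relies on close monitoring by the PI. Adverse events are collected in coaching sessions by an unblinded coach, so the handling of event reports would also need care to keep the arm out of what reaches the PI.

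2. **Drop the claim.** Delete the statement in Section 7.11 that the PI and co-investigators are blinded, and say that only the assessor is independent of delivery. This costs wording only. It gives up the safeguard, but the trial report will then not claim blinding that the trial did not have.
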